## Abstract

**Introduction:**

Breast cancer is globally the leading cancer in women, and despite the high 5-year survival rate the most frequent cause of cancer related deaths. Surgery, systemic therapy and radiotherapy are the three pillars of curative breast cancer treatment. However, locoregional recurrences frequently occur after initial treatment and are often challenging to treat, amongst others due to high doses of previous radiotherapy treatments. Radiotherapy can be combined with local hyperthermia to sensitize tumor cells to radiation and thereby significantly reduce the required radiation dose. Therefore, the combination treatment of mild local hyperthermia, i.e. locally heating of the tissue to 39-43°C, and re-irradiation with a reduced total dose is a relevant treatment option for previously irradiated patients. The mechanisms of this effect in the course of the therapy are to date not well understood and will be investigated in the HISTOTHERM study.

**Methods and analyses:**

Patients with local or (loco)regional recurrent breast cancer with macroscopic tumors are included in the study. Local tumor control is evaluated clinically and histologically during the course of a combination treatment of 60 minutes mild superficial hyperthermia (39 - 43°C) using water-filtered infrared A (wIRA) irradiation, immediately followed by hypofractionated re-irradiation with a total dose of 20-24 Gy, administered in weekly doses of 4 Gy. Tumor and tumor stroma biopsies as well as blood samples will be collected prior to treatment, during therapy (at a dose of 12 Gy) and in the follow-up to monitor therapy response. The treatment represents the standard operating procedure for hyperthermia plus re-irradiation. Various tissue and blood-based markers are analyzed. We aim at pinpointing key mechanisms and markers for therapy response which may help guiding treatment decisions in future. In addition, quality of life in the course of treatment will be assessed and survival data will be evaluated.

**Registration:**

The study is registered at the German Clinical Trials Register, Deutsches Register Klinischer Studien (DRKS00029221).

## Introduction

1

Breast cancer is by far the most common cancer in women, accounting for 24.5% of all cancer cases in women. It is the most common type of cancer worldwide with a global incidence of 47.8/100000*year, and the leading cause of cancer-related deaths in women worldwide (1). Overall 5-year survival rates of breast cancer patients are high (above 80%) in many countries (e.g. 88% in Germany, 89% in the USA), albeit with pronounced geographical differences (2). Survival strongly depends on the tumor stage and subtype at diagnosis (3). Local recurrence occurs in <2-10% of all patients after breast-conserving surgery and radiotherapy, and in 4% of cases after mastectomy within five years (4–10). Patients who suffer from a loco(regional) recurrence have an increased risk of dying from breast cancer compared to those without recurrence (11, 12).

According to guidelines, radiotherapy is an important curative treatment option for breast cancer in addition to systemic treatment and surgery (13). The conventional fractionation scheme entails a daily dose of 1.8-2.0 Gy/5x per week, up to a total dose of 50 Gy, potentially augmented with a local boost of the tumor bed. Hypofractionation and ultrahypofractionation schemes, e.g. with a total dose of 40 Gy and single doses of 2.67 Gy/5x per week or 27 Gy in five fractions within one week, have also proven to be safe and effective. These alternative regimens offer the advantage of significantly reducing the burden of treatment for the patients due to shorter duration of the therapy (7–10). Approximately 60% of patients, regardless of tumor stages, receive radiotherapy (3). In addition, radiotherapy plays a critical role in palliative care, addressing the needs of patients with advanced local and metastatic disease. In instances of locoregional recurrent disease, radiotherapy is frequently combined with chemotherapy to enhance radiosensitivity and to reduce the risk of systemic progression (14).

Radiotherapy may be combined with mild locoregional hyperthermia (HT), i.e., the local heating of the tumor-bearing tissue to 39°C – 43°C (4, 15), administered before or after radiotherapy (16, 17). A non-invasive method for heating superficial malignant tissue is the application of the water-filtered infrared A (wIRA) irradiation to the treated tumor area (17). This method results in peak temperatures (~ 42°C) in the superficial layers of the skin. In 20 mm of tissue depth, wIRA can yield temperatures of approximately 40°C (17–19).

Mild hyperthermia causes radiation sensitization of tumor cells by (a) improving tissue oxygenation (20), (b) inhibiting DNA repair mechanisms and (c) stimulating the immune system without causing direct cytotoxic effects in normal tissue (15, 16). In addition, hyperthermia at temperatures >42°C for a longer exposure time leads to direct cytotoxicity of hypoxic and nutrient-deprived cells (21, 22). These effects on radiosensitivity have been demonstrated to be most prominent with a very short time interval between hyperthermia and irradiation (23). Therefore, we apply radiotherapy within <5 minutes after hyperthermia. This approach ensures the effective utilization of hyperthermia-associated tissue oxygenation. By employing this combination treatment strategy, local tumor control can be achieved with a significantly lower radiation dose than with radiotherapy alone, allowing effective and tolerable treatments even after multiple prior irradiations of the affected body region (16, 24–26). Hyperthermia combined with radiotherapy offers a treatment option for patients for whom neither surgery nor conventional fractionated radiotherapy is an appropriate or effective treatment option, and for patients with otherwise treatment-resistant tumors. The likelihood of achieving a complete remission with HT + re-irradiation is inversely correlated to tumor extent (16, 27). wIRA hyperthermia combined with a hypofractionated re-irradiation scheme of 5x 4 Gy/week, administered immediately after hyperthermia, has demonstrated very high success rates in breast cancer patients with recurrent disease (16, 19). At the same time, weekly treatment sessions may alleviate the treatment burden for patients (16, 19).

Predictive histologic and/or molecular markers, as used in systemic treatment (28), have not yet been identified for hyperthermia. The clinical potential of predictive markers for hyperthermia lies in patient-tailored therapy, which may include decision support for treatment escalation or de-escalation. Furthermore, the identification of predictive markers offers the opportunity to infer previously unknown mechanistic processes that are affected by the combination therapy. In particular, immunological processes are considered to be relevant (29).

In the HISTOTHERM study, clinical and histological tumor control rates in patients with locally advanced recurrent breast cancer will be analyzed over time, as well as the tolerability of the therapy and the quality of life of the patients during the treatment. In addition, our study intends to identify potential markers and processes which play a role in the combination treatment. These may help to define markers that could guide treatment decisions in the future. Finally, the study will allow the longitudinal observation of histological and cellular changes.

## Methods and analysis

2

### Study design

2.1

The HISTOTHERM study is a monocenter, prospective, non-interventional, longitudinal study taking place at the Department of Radiation Oncology, Medical Center – University of Freiburg. Trial sponsor is the Medical Center – University of Freiburg, Germany. Due to ethical reasons for non-existing further treatment options, patients are not randomized to treatment versus control conditions (30). The general scheme of the study is presented in **Figure 1**. Patient recruitment and treatment takes place at the Department of Radiation Oncology, Medical Center – University of Freiburg, Germany. Tissue samples are processed, and proteomic analysis is performed in the Department of Clinical Pathology, Medical Center – University of Freiburg. The Departments of Radiation Oncology and Pathology are part of the Comprehensive Cancer Center Freiburg (CCCF) and the diagnostics laboratory of the pathology is accredited according to DIN EN ISO/IEC 17020:2012. Blood is analyzed at the Klinikum rechts der Isar of the Technical University Munich (TUM), Germany. Patient recruitment is ongoing since 11/2019 and end of recruitment is expected by 2025. We wrote our report guided by the SPIRIT checklist (31).

**Figure 1 f1:**
[figure not shown]
Schematic representation of the study design.

### Patients

2.2

Patients with local or (loco)regional recurrent (LRR) breast cancer after mastectomy, who present at the Department of Radiation Oncology at the Medical Center – University of Freiburg, Germany or in the interdisciplinary breast cancer tumor boards, will be screened for participation in the study. Patients with locoregional disease as classified according to the r-classes I-IV defined by Notter et al. (16) are eligible for the study. Central inclusion criteria is the indication for local mild superficial hyperthermia applied by wIRA combined with low-dose re-irradiation, i.e., patients with inoperable LRR that have a maximum depth extension of 20 mm. In addition, patients must (1) provide written, informed consent prior to enrollment and (2) be >18 years of age. Age <18 years, intolerance to local anesthetics, pregnancy, and lack of capacity to consent are exclusion criteria for this study. Distant metastases do not represent an exclusion criterion since they are common in patients with unresectable, locoregional recurrent breast cancer. Written informed consent was approved by the local ethics committee and will be obtained by the principal investigator from patients after sufficient time to read the patients’ information and discuss any questions. Informed consent to use biomaterial and associated data is collected using the informed consent form of the Center for Biobanking, Medical Center – University of Freiburg. Expected recruitment rates are high (>90%).

### Interventions

2.3

Patients enrolled in the HISTOTHERM study are treated according to the standard operating procedure for the combination treatment of hyperthermia and radiotherapy at the study center. The area to be treated is irradiated with 20 Gy in single doses of 4 Gy every 7 days, immediately (i.e., within 2-5 min) after application of local hyperthermia, for 5 consecutive weeks in general. Radiation treatment planning is conducted based on computer tomography (CT) scans, with 8-10 mm expansion of clinical target volume (CTV) to obtain planning target volume (PTV). The choice between electron fields or volumetric modulated arc therapy (VMAT) plans is determined by the patients’ anatomy. To ensure precise positioning for VMAT plans, cone beam CT is used for correct patient alignment. Furthermore, surface optical scanning is employed to monitor and verify patient positioning accuracy. No RT-boost is applied. Re-planning is done if clinically indicated. Superficial hyperthermia is applied with thermography-controlled wIRA using the TWH 1500 wIRA-hyperthermia system (Hydrosun^®^, Müllheim, Germany) in order to locally heat the tissue volume to be irradiated to a temperature of 39°C-43°C for 60 minutes. Superficial tissue temperatures are thermography-monitored and automatically recorded as a treatment protocol. This documentation contains both temperature curves and thermographic images for each minute of treatment. Prior to the first treatment session, a punch biopsy is taken to confirm the initial diagnosis and to re-assess the histologic profile of the tumor. The biopsy is performed under local anesthesia using a 2.0 mm-3.0 mm disposable biopsy punch. The size of the punches is selected to obtain sufficient material without suturing the wound. Blood is collected from eligible patients using aseptic techniques in EDTA blood collection tubes (9 mL).

Treatment response is clinically evaluated and (photo-)documented weekly during the course of the treatment. At a dose of 12 Gy, a second punch biopsy is taken from the same tumor lesion for diagnosis of treatment response by evaluating tumor cell quantity and proliferation. Where applicable, another blood sample is taken. In case of a continuously high density of intact tumor cells and/or a high proliferation rate, a sixth treatment session may be considered to increase the total dose to 24 Gy. The success of the treatment is clinically evaluated at a follow-up appointment 6 weeks after completion of treatment. Another punch biopsy is taken to evaluate the histologic response and another blood sample will be drawn for further analysis. Clinical follow-up continues at 3-months intervals for one year, followed by 6 months intervals up to 5 years.

The total radiation dose administered may need to be adjusted on an individual basis. Patients who cannot continue treatment due to generalized progression or other reasons may receive a total dose of less than 20 Gy. When possible, these patients are monitored for treatment response and follow-up is performed as scheduled.

Furthermore, questionnaires are employed to assess patients’ individual quality of life before and during therapy and at the first follow-up appointment. This assessment is conducted using a standardized quality of life questionnaire sourced from the European Organization for Research and Treatment of Cancer (EORTC), EORTC QLQ-C30 (32), and an additional study-specific module on the tolerability of hyperthermia.

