#### Identification of predictive markers and affected histological and cellular processes

2.4.3

Our overarching objective involves the discernment of tumor characteristics and the elucidation of a mechanistic basis underpinning responses to or resistance against the therapeutic intervention. Therefore, secondary outcomes of the HISTOTHERM study are the characterization of histologic and cellular differences within subgroups of patients to determine markers and key regulated processes involved in or activated by the combination therapy. To achieve these goals, comprehensive immunohistological and proteomic analyses on tissue and blood-based analyses will be undertaken.

Residual diagnostic tissue samples collected pre-treatment, during treatment (dose of 12 Gy) and at follow-up are used for analyses. Where available, tissue from the primary diagnosis is included in the analysis. Biopsies are routinely paraffin-fixed and embedded, followed by cutting of all required sections. After completion of routine diagnostics, study-specific immunohistochemical staining will be carried out on Formalin-fixed Paraffin Embedded (FFPE) tissue by trained staff of the CCCF biobank to obtain a comprehensive picture of the core processes involved.

Among the principal foci of investigation are the regulatory dynamics of the immune system, the mechanisms underpinning apoptosis and senescence. Approximately 20 different antibodies will be deployed for immunostaining of key proteins involved in those processes. Immunostaining will be performed in a standardized manner on multiple samples in parallel and will always include positive and negative controls to identify confounding staining effects. Subsequently, sections will be digitized and electronically archived on internal servers for further analysis.

Histologic sections are analyzed by trained staff who are blinded to clinical outcome. Depending on the marker protein under investigation, we will quantify and evaluate staining pattern, tissue distribution, intensity and number of positive and negative cells. Image analysis is supported by digital analysis tools, such as QuPath, which was developed specifically for pathological analysis (38). The tissue separation and cell detection tools are used for image classification and quantification of staining intensity, percentage of positive and negative cells and antibody distribution. Positively stained tissue structures are counted manually.

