We will conduct a two-fold analysis of protein expression patterns, firstly focusing on alterations during the course of the treatment, and secondly comparing expression between patient groups displaying varying treatment responses. Histologic and clinical regression will be statistically correlated with the histopathologic findings. In pursuit of predictive histologic markers for therapy response, we will perform rate modeling using Poisson regression with offset and exploratory factor analysis. Cluster analysis will be employed to identify relevant biological processes in the tissue. The identified proteins and processes will lay the foundation for further investigations for therapy prediction.

Further, mass spectrometry-based proteomics is used to identify proteome alteration from the limited biopsy material. Proteome profiling by liquid chromatography – tandem mass spectrometry is performed essentially as described in our recent benchmarking study (39). From the biopsies before and if applicable during treatment and from the primary diagnosis, 1-2 sections of 10 μm section thickness will be prepared for proteomic analysis after micro- or macrodissection and measured on a Q-Exactive+ high performance mass spectrometer. Due to the scarcity of sample material, we focus on abundance proteomics. Data-independent acquisition with label-free quantification will be used.

We expect a proteome coverage in excess of 3000 proteins measured in our micro- or macrodissected tissue slides. For analyses, we will consider proteogenomic probing of common genomic alterations. Statistical evaluation will involve supervised and unsupervised approaches. Hierarchical clustering will be employed to identify proteomic subgroups, and algorithms that are tolerant for a low frequency of missing values will be considered. Protein expression will be associated with outcome data using multivariate Cox-type analyses, including consideration of boosting steps if required. We will also consider multivariate linear models, as highlighted by linear models of microarray analysis, including consideration of variable selection by tools such as elastic nets. Multiple testing correction will be considered. The proteomic profiles will be correlated with treatment stage and success to identify potential protein markers indicating a particularly good or poor response.

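### No described analysis asks whether a 12 Gy marker adds to the clinical rating already available at that time, so a marker that only mirrors visible regression could be listed as predictive

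*Protocol article*

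**What the plan says.** **Clinical rating.** Section 2.3 of the protocol article: "Treatment response is clinically evaluated and (photo-)documented weekly during the course of the treatment". Section 2.4.2 adds that the rating follows RECIST-like categories and is the investigator's own assessment by inspection, photographs and palpation, because imaging is not routine during treatment.

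**12 Gy samples.** In section 2.3, "a second punch biopsy is taken from the same tumor lesion for diagnosis of treatment response by evaluating tumor cell quantity and proliferation". For blood, "Where applicable, another blood sample is taken".

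**Use in the marker search.** Section 2.4.3: "Residual diagnostic tissue samples collected pre-treatment, during treatment (dose of 12 Gy) and at follow-up are used for analyses". Proteomics uses the on-treatment biopsy only if applicable. The same section proposes circulating Hsp70 and tumor cell counts during therapy as predictors, and seeks an immune-cell signature that might predict clinical outcome.

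**Analyses described in section 2.4.3.**
- For tissue findings: "Histologic and clinical regression will be statistically correlated with the histopathologic findings"
- For the proteome: "The proteomic profiles will be correlated with treatment stage and success to identify potential protein markers indicating a particularly good or poor response"
- For the histologic marker models: "In pursuit of predictive histologic markers for therapy response, we will perform rate modeling using Poisson regression with offset and exploratory factor analysis"
- Cox-type and linear multivariate models are also named, without a covariate list.

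**Intended use.** The Introduction says the clinical potential of predictive markers may include "decision support for treatment escalation or de-escalation". Section 2.4.3 treats the proteins found as a basis for further work, and section 2.5 calls the study exploratory.

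**The concern.** By 12 Gy, patients can already differ in visible regression, and that regression is an early part of the response recorded later. The 12 Gy punch is itself read for response, through tumor cell quantity and proliferation. A tissue, proteome or blood marker that simply follows regression will therefore correlate with later response even if it carries no further information.

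This does no harm to a description of mechanism. It matters for decision support, where the question is what the sample tells a clinician who has already examined the patient. A direct association between marker and response does not answer that question. With about 20 antibodies and more than 3000 proteins expected, the candidate list could hold many stand-ins for shrinkage that inspection and palpation already show, and follow-up work could be steered towards them.

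Pre-treatment markers are not affected, because no treatment response exists when they are measured.

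**Working it through.** **The plan's own arithmetic.** Section 2.5: (3 biopsies + 1 earlier tissue sample) × 20 antibodies = 80 sections per patient, and 80 × 40 = 3200. This reproduces. The article gives no alpha, power or effect size, so none of its figures bears on this point. The rest is an illustration on assumed correlations.

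**Inputs.** n = 40 (section 2.5) and four response categories (section 2.4.2). Assumed: the correlations, the reliability of the rating and the spread over categories.

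**Model.** E is true regression at 12 Gy, standard normal. Marker M = a·E + noise and later response F = b·E + noise, both with unit variance, so M tells nothing about F beyond E. The rating C measures E with reliability ρ. F and C are cut into four categories.

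**Tests, two-sided 5%.** Unadjusted: rank correlation r(M,F). Adjusted: the partial rank correlation, [r(M,F) − r(M,C)·r(C,F)] / √{[1 − r(M,C)²]·[1 − r(C,F)²]}, with n − 3 = 37 degrees of freedom.

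**Expected values before categorising.** Unadjusted, the correlation is a·b. Adjusted, it is a·b·(1 − ρ) / √[(1 − a²ρ)(1 − b²ρ)]. For a = b:

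| a = b | unadjusted | adjusted, ρ = 1 | adjusted, ρ = 0.7 |
|---|---|---|---|
| 0.3 | 0.09 | 0 | 0.027/0.937 = 0.03 |
| 0.5 | 0.25 | 0 | 0.075/0.825 = 0.09 |
| 0.7 | 0.49 | 0 | 0.147/0.657 = 0.22 |

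An imperfect rating leaves part of the association in place.

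**Simulated share of studies significant (10,000 runs per setting, equal-sized categories).**

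| a = b | unadjusted | adjusted, ρ = 1 | adjusted, ρ = 0.7 |
|---|---|---|---|
| 0.3 | 8% | 5% | 6% |
| 0.5 | 30% | 6% | 10% |
| 0.6 | 55% | 7% | 16% |
| 0.7 | 83% | 8% | 31% |

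**Ratings bunched.** If about 75% of patients share one category, ρ = 0.7 and a = b = 0.7, the adjusted rate is about 41% to 48%, depending on where the other categories are cut. At ρ = 1 with the same bunching it is about 30%. The 5% to 8% therefore needs a rating that is both error-free and well spread.

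**Continuous response and rating, as a cross-check.** Unadjusted 15% (a = 0.3, b = 0.5) to 91% (a = b = 0.7); adjusted about 5% at ρ = 1 and 6% to 28% at ρ = 0.7. With 30 evaluable patients: 12% to 82%, about 5%, and 6% to 22%.

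**Price for a marker that does add information.** With a = b = 0.5, a direct marker effect of 0.3 and an error-free rating, detection falls from about 84% unadjusted to about 42% adjusted; other runs of similar settings gave 83% to 87% falling to 50% to 54%. Part of the fall is the shared regression being taken out, but the loss for a 40-patient screen is real.

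**The case against.** **The article does not exclude the rating.** A reader might infer that the plan deliberately leaves it out. The text does not support that. Section 2.4.3 names families of methods and lists no covariates, section 2.4.5 mentions three further Cox variables without naming them, and a full protocol or SAP may specify them. This stands, and the point is limited to what is described. What remains is that the described analyses relate markers to response and none is framed as a comparison with the examination.

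**The study is exploratory.** A reader might also infer that a shrinkage proxy would become a guide to treatment. The article says only that markers may help in future and are a basis for further investigation. This stands too: the risk is a misleading candidate list, not a changed treatment rule.

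**The comparator is debatable.** The one decision described at 12 Gy, whether to consider a sixth session, rests on histology and not on the clinical category. The routine histologic reading is also in hand by then, and a sixth session could alter the later response. So adjusting for the clinical category is not a clean test of added value. It is still informative, because that rating needs no biopsy.

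**The simulation builds in its answer.** Marker and response are independent given regression by construction, so an error-free adjustment must work. This is true; the figures show the possible size, not what this study will find. At correlations of 0.3 there is little to correct.

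**Nothing is lost.** The rating is collected, so the comparison can be added at any time. This is correct, and it means the study can still answer the question.

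**Conclusion.** The point holds as a gap in the question the described analyses answer. The article collects a weekly clinical rating, brings 12 Gy samples into the search for predictive markers and names decision support as a use, but describes no analysis of what those markers add to the rating.

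The size depends wholly on assumed correlations, from negligible at 0.3 to severe at 0.7. Adjustment helps in every setting examined but is incomplete when the rating is imperfect, which is plausible for an assessment without imaging. It would be wrong to conclude that one covariate settles the matter, or that a marker failing the adjusted test is worthless.

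Two readings are inferred. First, a rating is available at the 12 Gy sampling visit, which follows from weekly assessment but is not stated. Second, the response of interest is the one at 6 weeks, when section 2.3 evaluates treatment success; section 2.4.2 does not fix the time point for grouping patients.

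**What to change.** In section 2.4.3, for markers from 12 Gy tissue (including the proteome where measured) and 12 Gy blood only:

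1. Report the association with 6-week response twice, in the same patients: without adjustment, and with the clinical category rated at 12 Gy as one ordered covariate. Give estimates and intervals for both.
2. Describe markers whose association disappears after adjustment as correlates of a response already under way, not as shown to add to the examination.
3. Do not discard markers on the adjusted p-value alone. State that the rating is imperfect and that adjustment removes only part of the shared regression.

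Keep the unadjusted analysis for the mechanistic description of change. Pre-treatment markers need no such term.

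The cost is one more result column and one degree of freedom, with no new data collection. The downside is wider intervals and a substantial loss of power for the adjusted result in 40 patients, which is why it should inform the wording and not act as a filter.

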### Sample size calculation

2.5

Due to the exploratory nature of the study and for pragmatic reasons (63), 40 patients will be prospectively enrolled in the study. From each included patient, three biopsies will be taken and tissue from primary diagnosis or recurrence will be analyzed. Specimen staining is envisioned using approx. 20 antibodies. This results in 80 histological sections per patient to be processed and evaluated, and a total number of up to 3200 specimens to be examined. For proteome profiling our benchmarking study has highlighted that proteome alterations (e.g. between "responders" and "nonresponders”) are detectable with this sample size even in the presence of inter-individual proteome heterogeneity (39).

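### Marker groups are formed from response alone, so a patient who stopped below 20 Gy and did not regress is grouped with patients who completed treatment and did not respond

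*Protocol article*

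**What the plan says.** All of this is in the protocol article.

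- **Radiation delivered.** The general course is given as "The area to be treated is irradiated with 20 Gy in single doses of 4 Gy every 7 days" (Interventions). The same section allows two departures. A sixth session, to 24 Gy, may be considered when the biopsy at 12 Gy still shows many intact or proliferating tumor cells. In the other direction, "Patients who cannot continue treatment due to generalized progression or other reasons may receive a total dose of less than 20 Gy". Patients in the second group continue to be assessed for response and followed up where feasible.
- **Heat delivered.** The target is 39 to 43°C for 60 minutes. "Superficial tissue temperatures are thermography-monitored and automatically recorded as a treatment protocol", with a reading for each minute. On depth, the Introduction says: "In 20 mm of tissue depth, wIRA can yield temperatures of approximately 40°C".
- **Grouping.** Section 2.4.2 groups patients by clinical and histologic response in order to compare molecular profiles and survival.
- **Marker analyses.** Section 2.4.3 seeks the mechanism "underpinning responses to or resistance against the therapeutic intervention". It names Poisson regression with an offset, factor and cluster analysis, Cox-type models, linear models and elastic nets, and adds: "The proteomic profiles will be correlated with treatment stage and success to identify potential protein markers indicating a particularly good or poor response". It names no delivered dose, number of sessions or thermal measure, and states no rule for incomplete courses.

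**The concern.** Resistance to a treatment can be inferred only in someone who received it. The grouping rule looks at outcome alone, so it cannot separate a tumor that withstood the full course from one that had part of it. Two errors can follow.

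- **Mimicry.** Generalized progression is a stated reason for stopping, and distant metastases are not an exclusion (Patients). Early stopping is therefore likely to go with aggressive systemic disease. A marker of that disease would be more frequent among early stoppers and could surface as a marker of resistance to hyperthermia plus re-irradiation.
- **Dilution.** A genuine resistance marker is weakened if part of the non-responder group failed for another reason.

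The study's purpose is to pass candidate markers on to later work. A marker with the wrong meaning costs more there than one that is merely imprecise.

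**Working it through.** **The plan's own figures.** The sample size has no statistical derivation: "Due to the exploratory nature of the study and for pragmatic reasons (63), 40 patients will be prospectively enrolled in the study". The one figure that can be rebuilt is the section count: (3 biopsies + 1 earlier tissue) × 20 antibodies = 80 per patient, and 80 × 40 patients = 3200. This matches "a total number of up to 3200 specimens to be examined". Nothing in the article gives the expected number stopping below 20 Gy or the expected response rate.

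**Inputs.** N = 40 is from the article. Everything else is assumed: a split of 28 responders to 12 non-responders or 20 to 20; u early stoppers, all in the non-responder group; one marker, t-test at two-sided 5%; SD of 1.

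**1. Mimicry.** The marker is unrelated to local response but is raised by s in early stoppers. The non-responder mean then shifts by s × u / n(non-responders). For 28/12, u = 4 and s = 1, this is 1 × 4/12 = 0.33 SD. Rejection rates from 20,000 simulated trials:

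| u | 28/12, s = 1 | 28/12, s = 1.5 | 20/20, s = 1 | 20/20, s = 1.5 |
|---|---|---|---|---|
| 2 | 7.1% | 9.3% | 5.3% | 6.0% |
| 4 | 14.4% | 24.3% | 7.5% | 11.2% |
| 6 | 26.5% | 50.0% | 12.5% | 20.9% |
| 8 | 44.1% | 76.4% | 19.7% | 35.7% |

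With the early stoppers set aside, every cell returns to about 5%.

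**2. Dilution, harsher assumption.** A true resistance marker differs by 1 SD, and the early stoppers carry the responders' marker level. The observed difference is d = 1 − u / n(non-responders). Power comes from the non-central t distribution with non-centrality d × √(n1 × n2 / (n1 + n2)). For 28/12 the root is √(336/40) = 2.898. Setting the early stoppers aside restores d = 1 but leaves 12 − u non-responders.

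| u | d observed | Power, mixed (28 v 12) | Power, set aside (28 v 12 − u) |
|---|---|---|---|
| 0 | 1.00 | 0.81 | 0.81 |
| 2 | 0.83 | 0.65 | 0.75 |
| 4 | 0.67 | 0.47 | 0.68 |
| 6 | 0.50 | 0.29 | 0.58 |

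**3. Dilution, milder assumption.** The early stoppers are instead a random mix of true types, with responder share q = n(responders) / (40 − u). With f = u / n(non-responders), the observed difference is (1 − f) + f × (1 − q). For 28/12 and u = 4: q = 28/36 = 0.778, giving 0.667 + 0.333 × 0.222 = 0.741. By the normal approximation, power at 28/12 falls from 0.83 to 0.72, 0.57 and 0.40 with u = 2, 4 and 6. At 20/20 it falls from 0.89 to 0.85, 0.80 and 0.74.

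**4. Why total dose is not a simple covariate.** Delivered dose can be below 20 Gy because the patient progressed, and 24 Gy because the biopsy at 12 Gy looked poor. Low and high dose can both go with poor disease, and the high dose is itself a consequence of interim response. A linear dose term would not remove the problem and could add bias.

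**The case against.** The strongest reply has five parts.

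- **No text classes early stoppers as resistant.** Correct. A reader might infer that under-treated patients are placed in a resistant group by rule. The article does not say so. Such a patient may respond, be stable, or lack the six-week biopsy and so have no histologic grade, which is a missing-data matter. The point holds only for those who are assessed and do not regress.
- **The article is condensed.** The Poisson offset is unnamed, as are the three extra Cox variables in the survival section, and a full protocol or SAP may name dose or heat. It therefore cannot be asserted that exposure is never used. What stands is that the article does state the grouping rule and does keep early stoppers in assessment. An offset or a survival covariate would not change a response label already given.
- **The heat argument is thin.** A reader might infer that patients differ greatly in heating, or turn the 39 to 43°C range into a large ratio of thermal effect. The article supports neither. The range is a target, the 42°C and 40°C figures describe a gradient with depth, and the ratio would need a conversion factor the article does not give. The recordings are also superficial, while lesions may extend to 20 mm. This limits heat to an exploratory description.
- **Restricting to completers has its own bias.** It selects on a post-baseline event tied to progression, and all the loss falls on the smaller group. This stands, and is why the restricted analysis should accompany the full one and not replace it.
- **The study is exploratory and small.** True, and it limits the weight of the point. It does not alter what a candidate marker would be taken to mean.

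**Conclusion.** The point holds in a limited form. Grouping by response alone, with early stoppers kept in assessment, lets failure after an incomplete course be read as resistance, and the named reason for stopping gives that error a direction. Its size is unknown because the article gives no count. Under the assumptions above it is small with about 2 such patients: at most a 9% false-positive rate, and at 28/12 power of 0.65 to 0.72 against 0.81 to 0.83. It is serious with 6 or more in a non-responder group of about 12: a false-positive rate of 27% or higher, and power of 0.40 or lower. Balanced groups soften it. Setting early stoppers aside gave more power than mixing them under the harsher dilution assumption (0.68 v 0.47 with 4 of 12), despite the smaller group. Only N = 40 comes from the article; the split, the effect sizes and the number affected are illustrations.

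**What to change.** In section 2.4.3:

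1. Run each marker-response comparison twice: in all assessed patients, and excluding those who did not complete the general 20 Gy course. Report how many patients are excluded and how their response was classified.
2. Call a marker a resistance marker only if its direction and approximate size hold in both analyses. Significance in both should not be required, because the restricted set is smaller.
3. Do not adjust for total dose as a simple covariate, and say why: a total of 24 Gy may itself result from a poor biopsy at 12 Gy.
4. From the recorded curves, derive one surface-temperature summary per patient, defined in advance (for example, the mean over sessions). Report it by response group as an exploratory exposure measure, noting that it describes superficial tissue only.

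The cost is analysis wording, one derived variable and a second run of each comparison, all from data already recorded. The downside is a smaller non-responder group in the restricted analysis, with less precise estimates. Treatment and visits are unchanged.
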